### Primary analysis

To evaluate feasibility, we will estimate recruitment rate, assessment completion rate, and treatment attendance rate by sample proportions and provide their standard errors based on binomial distribution. We will evaluate acceptability by assessing patient satisfaction (CSQ scores) repeatedly over time (baseline, 6 months, and 12 months). We will analyze improvement in patient satisfaction by a linear mixed-effects model with random subject-specific intercepts to handle correlation between repeated measurements of the outcomes. We will include time as predictor of interest. Significance of improvement in satisfaction over time will be assessed by testing whether the slope of time is zero.

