### Quantitative analysis

All tests will be two-sided and performed at significance level α = 0.05.

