### Precision analysis

Since this is a pilot study for a future large randomized trial, we did not conduct a power analysis in accordance with recommendations in the new National Institutes of Health guidelines http://grants.nih.gov/grants/guide/pa-files/PAR-09-173.html and Kraemer and Kupfer [63]. Instead, we conducted precision analysis for the main study outcomes--feasibility and acceptability--by computing margin of error of an estimated rate to assess the precision that can be achieved by the proposed sample size. Margin of error is half the width of a confidence interval of an estimator. The smaller the margin of error, the tighter the confidence interval and the more precision we achieve for an estimator. We used the original PCARE [18] study treatment and completion assessment rates to estimate standard errors and margins of errors. PCARE's observed treatment completion rate was 0.68, with a sample size of 30, the standard error was 0.085 and the margin of error was 0.167. PCARE's observed assessment completion was 0.78 at 6 months and 0.69 at 12 months, the corresponding standard error is 0.076 and 0.084, respectively, and the margin of error is 0.15 and 0.17, respectively. For the CSQ scores (acceptability measure), when the standard deviation of the improvement of CSQ is 1, 2, or 4 points, the corresponding margin of error for estimating mean improvement is 0.18, 0.36, and 0.72, respectively. In all, our precision analysis indicates we have small margin of errors for each of our main study outcomes.

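### The feasibility margins for treatment and assessment completion are Wald half-widths at n = 30; the implied 95% interval covers about 93% on average, and a Wilson interval is a nearly free improvement

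*Protocol article*

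**What the plan says.** Feasibility is one of the two primary outcomes of the pilot (Phase IV). For its three rates, the Primary analysis section plans to estimate "recruitment rate, assessment completion rate, and treatment attendance rate by sample proportions and provide their standard errors based on binomial distribution". That standard error is the only measure of uncertainty named for them. Confidence intervals are promised only for the outcomes in the Exploratory analysis section, where no method is named.

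The Precision analysis section shows how the standard error is used. It defines its yardstick: "Margin of error is half the width of a confidence interval of an estimator". It then gives figures for two kinds of completion rate, taken from the earlier PCARE trial:

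- Treatment completion: "PCARE's observed treatment completion rate was 0.68, with a sample size of 30, the standard error was 0.085 and the margin of error was 0.167".
- Assessment completion: "PCARE's observed assessment completion was 0.78 at 6 months and 0.69 at 12 months", for which "the corresponding standard error is 0.076 and 0.084, respectively, and the margin of error is 0.15 and 0.17, respectively".

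The section gives no margin for the recruitment rate. Phase IV bases that rate on 69% in PCARE, with at least 45 patients to be screened. The working level is set in the Quantitative analysis section: "All tests will be two-sided and performed at significance level α = 0.05".

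**The concern.** An interval formed as estimate plus or minus 1.96 estimated standard errors is known to perform poorly for proportions in small samples when the rate is away from 0.5. It is centred on the observed proportion, and its estimated standard error shrinks as that proportion approaches 1. A favourable chance result therefore gets an interval that is both high and short. For a pilot meant to inform a larger trial, the informative end is the lower limit, because it says how poor completion might be. That is the end that is set too high. A reader given only the proportion and its standard error would naturally form the same interval.

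**Working it through.** **Inputs.** n = 30 and rates 0.68, 0.78 and 0.69 (Precision analysis); two-sided level 0.05, so z = 1.96 (Quantitative analysis); recruitment 0.69 with at least 45 screened (Phase IV).

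**Step 1: reproduce the plan's figures.** SE = sqrt(p(1-p)/n); margin = 1.96 x SE.

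| p | SE | 1.96 x SE | Plan's SE | Plan's margin |
|---|---|---|---|---|
| 0.68 | sqrt(0.68 x 0.32/30) = 0.0852 | 0.167 | 0.085 | 0.167 |
| 0.78 | sqrt(0.78 x 0.22/30) = 0.0756 | 0.148 | 0.076 | 0.15 |
| 0.69 | sqrt(0.69 x 0.31/30) = 0.0844 | 0.165 | 0.084 | 0.17 |

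All agree after rounding, so the plan's half-widths are Wald half-widths.

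**Step 2: exact coverage.** For a true rate p, coverage is the sum of the binomial probabilities P(X = x), x = 0 to 30, over those x whose interval contains p. The Wilson interval, with q = x/n, has centre (q + z²/2n)/(1 + z²/n) and half-width z x sqrt(q(1-q)/n + z²/4n²)/(1 + z²/n).

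| True p, n = 30 | Wald coverage | Wald lower limit above p | Wald upper limit below p | Wilson coverage | Mean half-width, Wald / Wilson |
|---|---|---|---|---|---|
| 0.68 | 92.1% | 4.9% | 3.1% | 95.2% | 0.164 / 0.156 |
| 0.69 | 91.6% | 6.1% | 2.3% | 95.4% | 0.162 / 0.155 |
| 0.78 | 90.2% | 7.8% | 2.0% | 95.4% | 0.144 / 0.140 |

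The gap at p = 0.78 comes from a single count. With 27 of 30, q = 0.90 and SE = sqrt(0.9 x 0.1/30) = 0.0548. The Wald interval is 0.793 to 1.007, which misses 0.78. The Wilson interval is 0.744 to 0.965, which contains it.

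**Step 3: dependence on the rate.** Because counts are discrete, coverage jumps as p changes. Wald at n = 30 gives 94.5% at 0.67, 92.1% at 0.68, 95.3% at 0.70 and 88.8% at 0.79. At 0.70 Wilson is the lower of the two, at 93.0%. Averaging over true rates removes the jumps: over 0.60 to 0.80, Wald gives 92.8% and Wilson 95.1%.

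**Step 4: recruitment.** At p = 0.69 and n = 45, Wald coverage is 94.5%.

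**Step 5: effect on the intervals, observed rate equal to the planning rate.**

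| Rate | Wald | Wilson | Fall in lower limit |
|---|---|---|---|
| 0.68 | 0.513-0.847 | 0.501-0.818 | 0.012 |
| 0.78 | 0.632-0.928 | 0.605-0.891 | 0.027 |
| 0.69 | 0.525-0.855 | 0.511-0.826 | 0.014 |

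**The case against.** The sentence in Primary analysis is not wrong. The binomial standard error is the right standard error for a proportion, and no interval is promised there. The Precision analysis section is a planning calculation, for which 1.96 x SE is conventional, and an article may leave the choice of interval to a fuller document. This stands as far as it goes, and the absence of a named interval method is no finding. The point rests on what is printed: half-widths of a confidence interval computed as Wald, and the same standard error carried forward as the sole error measure.

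The size is also open to challenge. The 0.68, 0.69 and 0.78 come from a trial of the intervention as designed for nurses and before adaptation for Hispanic patients, so the true rates here will not equal them, and coverage changes sharply with small shifts. That is right, and the average of about 93% is the fairer summary.

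Three stronger readings are tempting and not supported:

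- A reader might infer that all three feasibility rates have 90% to 92% coverage. The recruitment rate has a denominator of at least 45 and comes close to nominal at 0.69.
- A reader might infer that the misses all lie on one side. At 0.68 the upper tail is 3.1%, also above 2.5%.
- A reader might infer that a feasibility decision would change. The documents set no threshold or go/no-go rule, and each shift in the lower limit is less than one patient in 30 (1/30 = 0.033).

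**Conclusion.** The point holds as a minor improvement. For treatment and assessment completion at n = 30, the Wald interval behind the stated margins covers about 93% on average over plausible rates instead of 95%. The shortfall comes mainly from a lower limit that is too high. Wilson restores average coverage to 95.1%, with slightly shorter intervals on average at the plan's three rates. The plan's arithmetic for these margins is therefore sound, and its statement about precision is not weakened by the change of method.

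This assumes independent patients and a yes/no outcome per patient over a denominator of 30. If treatment attendance were counted over sessions within patients, neither interval would apply as it stands. The average also assumes that true rates lie between 0.60 and 0.80, a range chosen to bracket the plan's three figures.

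**What to change.** In Primary analysis, state that the patient-level completion proportions will be reported with Wilson score 95% intervals, alongside the binomial standard errors if wanted. For consistency, report the recruitment rate in the same way on its own denominator of patients screened. In Precision analysis, give the planning intervals as Wilson: 0.50-0.82 at 0.68, 0.61-0.89 at 0.78 and 0.51-0.83 at 0.69.

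The cost is about one sentence and one line of code, with no extra patients or data. The downside is that the reported lower limits look slightly less favourable, and that the intervals are no longer symmetric about the estimate, so each must be given as two limits and not as a single margin.

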### Phase IV

This phase will complete IM step 6 (evaluation) with a single group, pre-post, 12-month open pilot study (N = 30) carried out at WHCS. Two SW CMs will deliver the modified intervention, each carrying a caseload of 15 patients. Thirty adult Hispanic patients with SMI will be recruited. Inclusion and exclusion criteria are identical to those in phase IV. Based on the PCARE study recruitment rate of 69%, we will screen at least 45 patients to achieve our recruitment goal. A bilingual RA will recruit patients at WHCS through flyers, canvassing of waiting rooms, word of mouth, and provider referrals. We have allocated 18 months to this phase, which provides a six-month cushion for unanticipated problems with recruitment and attrition. Descriptions of the proposed measures for this study are presented in Table 3. As part of the planning process for this phase, the CAB will assess the appropriateness of these outcome measures for the intended patient population and, if necessary, identify other culturally relevant measures for key constructs (*e.g.*, acculturation, health literacy, illness perceptions).

**Table 3 T3:** Description of measures

Construct	Measure description
Feasibility	Study recruitment, assessment completion, and treatment attendance rates
Acceptability	CSQ and postintervention focus groups. The CSQ is an eight-item questionnaire scored on a four-point Likert-type scale. Scores range from 8 to 32, with higher score indicating higher satisfaction [68]. The CSQ is available in English and Spanish [69] and has excellent internal consistency in Hispanics [70].
Patient activation	PAM-13, [71] a 13-item scale that assesses patients' knowledge, skills, and confidence about self-management. Scores range from 0 (no activation) to 100 (high activation). PAM-13 has strong psychometric properties, including content and construct validity [71], has been tested across a range of chronic illnesses [72,73], and is available in English and Spanish.
Receipt of preventive primary care	PCARE study measure drawn from the USPSTF guidelines [74]. A total of 23 indicators are examined across four domains: (1) physical examinations, (2) screening tests, (3) vaccinations, and (4) education. Scored based on patients' medical records and self-report at baseline, three months, and six months. An aggregate preventive services score calculates the proportion of appropriate services obtained [18].

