Health and mental health-related quality of life	SF-12 [75], a self-report measure available in English and Spanish and validated among adults with SMI that generates two summary scores for physical and mental health-related quality of life [76]. Summary scores range from 0 to 100, with higher scores reflecting better health.
Covariates	Demographics: *e.g.*, race/ethnicity, age, gender, education, and marital status Acculturation: nativity, language dominance, time in the United States, age of migration; the Bidimensional Acculturation Scale [77], a 24-item self-report measure that uses separate four-point scales to tap acculturation-related changes in two languages. Barriers to medical care: a list of 11 common factors that may prevent patients from seeking medical care [78,79]. Comorbid medical conditions: a list of 17 common medical conditions by patient self-report.

CSQ = Client Satisfaction Questionnaire; PAM-13 = Patient Activation Measure; PCARE = primary care, access and referral; USPSTF = U.S. Preventive Services Task Force; SF-12 = Short Form Health Survey; SMI = serious mental illness.

The primary outcomes of the pilot study are feasibility and acceptability. Two post-intervention FGs will be conducted with study participants to explore their reactions to the intervention. Each FG will be composed of 8-10 patients and follow the FG methods described in phase II. Although this is not an efficacy trial, we would be remiss in not taking this opportunity to initially explore the intervention's effect, as measured by patient activation, receipt of preventive primary care, and physical- and mental-health-related quality of life. Covariates include demographics, acculturation, barriers to care, and comorbid medical conditions. The RA will assess patients at baseline, 6 months, and 12 months. Self-report measures and medical chart abstractions will be obtained. Patients will be asked for consent to access medical records at WHCS and their primary care clinic. The RA will conduct these abstractions under [name]'s supervision.

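### The primary quantitative analysis of acceptability tests change in CSQ from a pre-intervention baseline, not how satisfied patients are with the programme once they have received it

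*Protocol article*

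**What the plan says.** All places are in the protocol article.

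- **Outcome status (Phase IV).** "The primary outcomes of the pilot study are feasibility and acceptability".
- **Design (Phase IV).** The evaluation is done "with a single group, pre-post, 12-month open pilot study (N = 30) carried out at WHCS", and "The RA will assess patients at baseline, 6 months, and 12 months".
- **Measure (Phase IV, Table 3).** Acceptability is measured by the CSQ and by post-intervention focus groups. For the CSQ, "Scores range from 8 to 32, with higher score indicating higher satisfaction".
- **Analysis (Primary analysis).** "We will evaluate acceptability by assessing patient satisfaction (CSQ scores) repeatedly over time (baseline, 6 months, and 12 months"). The model is a "linear mixed-effects model with random subject-specific intercepts", with time as the predictor of interest. "Significance of improvement in satisfaction over time will be assessed by testing whether the slope of time is zero". The section on missing data names the same model for the acceptability analysis.
- **Error level (Quantitative analysis).** "All tests will be two-sided and performed at significance level α = 0.05".
- **Precision (Precision analysis).** The CSQ target is again mean improvement, with margins of 0.18, 0.36 and 0.72 for SDs of 1, 2 and 4 points.
- **Other evidence.** Preliminary analyses promises descriptive statistics at each time point for variables relevant to the aims. Phase IV plans two post-intervention focus groups of 8 to 10 patients each, and Phase V integrates qualitative and quantitative findings.

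The article does not say which service the CSQ asks about at any visit.

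**The concern.** Acceptability of a programme is a level: how satisfied are the people who received it? The planned test answers a different question, namely whether satisfaction rose from a point before anyone had received it. The two can disagree in both directions. Patients who were content with the clinic beforehand and are equally content with the programme produce no slope. Patients who move from very dissatisfied to fairly dissatisfied produce a significant one. The upper bound of 32 adds to this: the higher the baseline score, the less room there is to improve, whatever patients think of the programme.

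The pilot is meant to guide refinement of the intervention and the design of a larger trial. If the headline quantitative result on acceptability is the slope, that work could start from a misleading summary.

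**Working it through.** **1. The plan's own CSQ figures.** The Precision analysis section defines the margin of error as half the width of a confidence interval. With n = 30:

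- Standard error = SD/√30. For SD 1, 2, 4: 0.18, 0.37, 0.73.
- 95% margin = 1.96 × SD/√30: 0.36, 0.72, 1.43.
- Stated margins: 0.18, 0.36, 0.72.

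The stated CSQ margins are about half of what the section's own definition gives; they are close to the standard errors. The feasibility margins do reproduce (for example, 0.68 gives SE 0.085 and margin 0.167). This is a separate slip, but it matters here because the CSQ precision has to be restated in any case, and because the section's target is improvement, not level.

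**2. What the baseline score can refer to.** The design is single-group pre-post, so baseline precedes the programme. The phase II eligibility criteria, which the pilot appears to share, require active patients of the clinic. There are two possibilities:

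- The CSQ asks about the care manager programme at 6 and 12 months. Then the slope compares ratings of two different services.
- The CSQ asks about clinic services throughout. Then the slope concerns one service, but that service is not specifically the programme.

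In neither case is the slope the acceptability of the programme to those who received it.

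**3. Level against slope.** Illustration with n = 30, visits coded −1, 0, 1, scores rounded and kept within 8 to 32, and 2,000 runs. Assumed between-patient SD is 3 and within-patient SD 2.83 (SD of change = 2.83 × √2 = 4, the largest value in the Precision analysis). The means are also assumed; the documents give none.

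| True means at 0, 6, 12 months | Level on the 8–32 scale | Slope test significant |
|---|---|---|
| 28, 28, 28 | high throughout | 4.7% |
| 14, 16, 18 | low throughout | more than 99% |

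Hand check of the second row: SE of the slope per visit = 2.83/√(2 × 30) = 0.365. The true slope is 2, so the expected test statistic is about 2/0.365 = 5.5.

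**4. Precision for the post-exposure mean.** The documents give no SD for this score. For assumed SDs of 2, 4 and 6, the margin 1.96 × SD/√n is:

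- n = 30: 0.72, 1.43, 2.15.
- n = 21 (0.69 × 30 = 20.7, the cited 12-month completion): 0.86, 1.71, 2.57.

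**5. Secondary and conditional: size of the slope test.** With three balanced visits, a random-intercept model uses the average of the three correlations, while the slope's true variance depends on the correlation between baseline and 12 months. The ratio of model SE to true SE is √((1 − average r)/(1 − r between 0 and 12 months)). All correlations below are assumptions.

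- Equal correlation: ratio 1, size 5%.
- 0.60 between adjacent visits and 0.55 across 12 months: average 0.583; √(0.417/0.45) = 0.96; size about 5.9%.
- AR(1) with 0.6: average (0.6 + 0.6 + 0.36)/3 = 0.52; √(0.48/0.64) = 0.866; size 9.0%.
- AR(1) with 0.5 and 0.7, by simulation: 8.5% and 9.4%.

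The range is about 5% to 9%.

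**The case against.** The best defence is that the plan contains more than the slope. Table 3 defines acceptability by the CSQ and by post-intervention focus groups, which ask directly about reactions to the intervention; Phase V then examines where the two sources disagree. CSQ means at 6 and 12 months should also appear in the per-visit descriptive statistics. All this stands, and it limits the harm. It does not remove the fault: the focus groups are qualitative, and the descriptive statistics are preliminary, with no interval and no status as the acceptability estimate.

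One could add that the planned model also yields fitted means after baseline. With linear time and complete data, however, the fitted 6-month mean is the average of all three visits, baseline included. Observed means of 20, 26, 26 (an illustration) would give a fitted 6-month value of 72/3 = 24.

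A reader might infer several stronger points that the article does not support:

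- **That the p-value decides whether the programme goes forward.** No progression rule is stated. The test is tied to improvement in satisfaction, and results are to be discussed with the advisory board.
- **That the slope certainly mixes two services.** The CSQ's referent is not given, so this is one of two possibilities.
- **That a straight line is wrong because a step followed by a plateau is expected.** Nothing in the article predicts that pattern.
- **That the test's error rate is 8.5% to 9.4%.** This needs AR(1) decay with a 6-month correlation of 0.5 to 0.7, and no correlation is reported.

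Nor is this a complaint about detail left to a fuller plan. It concerns a method that the article states explicitly.

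**Conclusion.** The point holds in a limited form. The plan makes acceptability primary and fixes its quantitative analysis as improvement in CSQ from a pre-intervention baseline, tested by a zero slope. That estimand is change in satisfaction, not acceptability of the programme among those exposed to it, and the two can point in opposite directions. This follows from the design and needs no assumption about the data. The contrast between 4.7% and more than 99% shows how far apart they can be, but rests on assumed means and SDs.

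The focus groups and per-visit descriptives soften the consequence, so acceptability would not be judged on the slope alone. What is missing is the post-exposure CSQ level, with an interval, as the primary quantitative estimate. The covariance issue is secondary: a size of about 5% to 9% depending on assumed correlations, and it bears only on an analysis of change.

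**What to change.** 1. Make mean CSQ at 6 months and at 12 months, each with a 95% confidence interval and read on the 8 to 32 scale, the primary quantitative estimate of acceptability, alongside the focus groups.
2. State which service the CSQ refers to at each visit.
3. Report change from baseline as exploratory change in satisfaction with care, and remove the zero-slope test as the acceptability criterion.
4. For any analysis of change, treat visit as categorical with an unstructured covariance.
5. Restate the Precision analysis for the post-exposure mean, at the expected number of completers and over a stated range of SDs, with margins that follow the section's own definition.

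Cost: mostly wording, with no additional visits. There would be no single p-value for improvement, and the questionnaire instructions may need a small change if the referent has to be made explicit.

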### Accounting for missing data in the analysis

If a patient drops out of the study, we will record the stated reasons for dropout and make all efforts to obtain a final assessment. Failing this, the end-of-treatment assessment will be the patient's last scheduled assessment. The analysis of acceptability as measured by the Client Satisfaction Questionnaire (CSQ) will be based on a multilevel model with subject-specific random intercepts. For analyses that include missing outcomes, PROC MIXED in SAS allows for continuous data that may be missing for some patients due to lack of completion of assessments. Measurement at each time point on each patient contributes to the analysis. Thus, complete outcome information for all patients at all sessions is not needed. For analyses that include missing covariates, we will use multiple imputation to account for missing data. The inferences from incomplete data are valid, provided the missing data are missing at random [59]. Unfortunately, this assumption is untestable in most medical research. When we suspect this assumption does not hold, we will assume a model for the missing mechanism that depends on the unobserved outcome value and do the analysis incorporating the assumed model and conduct sensitivity analysis [60-62].

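### The random-intercept-only model for the CSQ slope test assumes equal correlation between all visits; under decaying correlation or patient-specific slopes the 5% test would run at about 6-10%

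*Protocol article*

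**What the plan says.** Phase IV describes a "single group, pre-post, 12-month open pilot study (N = 30) carried out at WHCS". Its primary outcomes are feasibility and acceptability, and the quantitative measure of acceptability is the CSQ at baseline, 6 and 12 months.

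The section Primary analysis fixes the model: "We will analyze improvement in patient satisfaction by a linear mixed-effects model with random subject-specific intercepts to handle correlation between repeated measurements". Time is the predictor of interest, and improvement is assessed by "testing whether the slope of time is zero". The section on missing data repeats the choice: the CSQ analysis is "based on a multilevel model with subject-specific random intercepts". The section Quantitative analysis sets the level: "All tests will be two-sided and performed at significance level α = 0.05".

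Neither place names a random slope, a serial residual structure, an unstructured covariance or a robust standard error. No CSQ correlation, variance by visit or slope variance is given.

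**The concern.** A random intercept with independent residuals implies one common correlation for 0-6, 6-12 and 0-12 months. With three equally spaced visits and complete data, the estimated slope is simply the 12-month-minus-baseline contrast. The model does not estimate that contrast's variance from the contrast alone. It pools it with the variance of the curvature contrast, which is legitimate only if the two are equal.

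Two ordinary departures make the slope contrast the more variable of the two: correlation that weakens as visits move apart, and patients who change at different rates. The second is plausible over 12 months of individually tailored care management. Pooling then understates the standard error, so the interval is too narrow and improvement is claimed too often.

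This is the only hypothesis test that the article describes. It concerns a primary outcome, and the results are meant to inform a larger trial.

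**Working it through.** **Inputs from the article.** n = 30, one group; visits at 0, 6 and 12 months; two-sided alpha 0.05; random intercept only; linear slope. For dropout, the completion rates of the earlier PCARE trial quoted under Precision analysis: 0.78 at 6 months and 0.69 at 12 months.

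**Inputs that must be assumed.** The within-patient covariance of the CSQ. Its overall scale cancels out of the error rate.

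**Formula (complete data).** Let L = (Y12 - Y0)/√2 and Q = (Y0 - 2·Y6 + Y12)/√6. The random-intercept model estimates the variance of L by averaging var(L) and var(Q), on 2·30 - 1 = 59 degrees of freedom. Hence

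- SE ratio (model/true) = √[(var L + var Q)/(2·var L)]
- type I error ≈ 2·[1 - Φ(1.96 × ratio)]

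**The plan's own level.** With equal correlation 0.5, var L = var Q = 0.5, the ratio is 1 and the error is 0.050 (simulated 0.0503; 0.0509 with dropout). The stated 5% is reproduced when the model's assumption is true.

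**Worked departure.** AR(1) with adjacent correlation 0.5 and unit variance: var L = 1 - 0.25 = 0.75; var Q = (6 - 8·0.5 + 2·0.25)/6 = 0.417. The ratio is √(1.167/1.5) = 0.882, and 1.96 × 0.882 = 1.73, so the error is 0.084.

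| Assumed structure | SE ratio | Type I error, formula | Simulated, n = 30 |
|---|---|---|---|
| Equal correlation | 1.00 | 5.0% | 5.0% |
| AR(1), 0.3 | 0.92 | 7.1% | 7.0% |
| AR(1), 0.5 | 0.88 | 8.4% | 8.3% |
| AR(1), 0.7 | 0.85 | 9.5% | 9.5% |
| AR(1), 0.9 | 0.83 | 10.5% | 10.4% |
| Mild decay: 0.6 adjacent, 0.5 at 12 months | 0.93 | 6.8% | 6.9% |
| Patient slopes, variance 0.05 per 6 months* | 0.96 | 6.1% | 6.1% |
| Patient slopes, variance 0.10* | 0.93 | 7.0% | 7.0% |
| Patient slopes, variance 0.25* | 0.87 | 9.0% | 8.9% |
| 0.4 adjacent, 0.6 at 12 months | 1.15 | 2.4% | 2.4% |

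*Intercept variance 0.5, residual variance 0.5.

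**With completely random dropout at the quoted rates** (REML fit): AR(1) 0.5 gives 8.0%, 0.7 gives 9.5%, 0.9 gives 10.6%; mild decay 6.7%; slope variance 0.25 gives 10.0%.

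**Freed variance.** Testing the mean of patient-specific slopes (t on 29 df), with the slope variance estimated freely, gives a simulated error of 4.8-5.2% in every scenario. Its price when correlations are equal is the ratio of t quantiles: 2.045 (29 df)/2.001 (59 df) = 1.022, about 2% wider.

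**Linear time, checked separately.** Shift the 6-month mean by 0.5 SD with no net 12-month change. The error falls: from 8.3% to 6.3% under AR(1) 0.5, and from 5.0% to 3.4% under equal correlation 0.5. Curvature adds to the residual variance, so it enlarges the standard error. Its other effect is bias under dropout. With 22% and 31% missing and correlations of 0.3-0.7, an assumed 0/4/4 mean profile gives an expected 12-month change of about 4.2 (true 4.0), and 0/4/2 gives about 2.3 (true 2.0).

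**The case against.** The strongest reply has four parts.

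- **No document figure fixes the correlation.** This stands. A reader might infer that the test is known to run at 8-10%. That follows only from AR(1) correlation of about 0.5-0.8 or a large slope variance; mild departures give 6-7%. Nor does the error go only one way, as the 2.4% case shows.
- **The straight line is not to blame for a small standard error.** This also stands. A reader might attribute the problem to the linear term, but curvature makes the test more conservative. The bias of 0.2-0.3 points is small on a scale of 8 to 32. It is under half of the largest standard error implied by the article's own CSQ standard deviations (4/√30 = 0.73).
- **Little turns on the p-value.** This is an uncontrolled pilot of 30 patients, described as not an efficacy trial. It is planned on precision, supplements the CSQ with focus groups and has no go/no-go rule on the slope. This limits the weight of the point. It does not remove it, because the understated standard error also narrows the confidence interval.
- **Covariance detail belongs in an analysis plan that is not shown.** This stands for the degrees-of-freedom method. It does not answer the main point: the random-intercept choice is stated in two sections, and one of them gives it as the means of handling the correlation between visits.

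**Conclusion.** The point holds in conditional form. The stated model assumes equal correlation between all pairs of visits. If correlation decays with time or patients' slopes differ, the slope's standard error is about 4-17% too small (ratios 0.96 to 0.83), and the nominal 5% test at n = 30 runs at about 6-10%. It runs at 5% if correlations are equal, and below 5% if adjacent correlations are lower than the 12-month one. These figures rest on assumed covariances, because the article supplies none. The linear time term is a separate, minor issue. The change is worth making before analysis because the method is fixed in the text, bears on a primary outcome and is cheap to correct. In a pilot of this kind it is an improvement to make, not a fatal flaw.

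**What to change.** In Primary analysis, and in the matching sentence of the missing-data section, replace the random-intercept-only covariance with an unstructured 3x3 within-patient covariance (PROC MIXED, REPEATED with TYPE=UN) and Kenward-Roger degrees of freedom. Keep the planned test of the time slope. Optionally, also report the baseline-to-12-month contrast with its 95% confidence interval from a fit with visit as a factor, which drops the straight-line assumption.

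Name a fallback in advance. If the model does not converge, use a simpler structure that still allows unequal correlation, such as a random slope or heterogeneous AR(1). Uncorrected robust standard errors are not a good fallback, since they can themselves be too small with about 30 patients.

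The cost is a small change to code and text, six covariance parameters instead of two, and an interval about 2% wider if equal correlation turns out to be true. At the quoted completion rate, about 21 patients (0.69 × 30 = 20.7) would inform the 12-month terms, which is why the fallback should be written down.
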